**Figure 3 figure3:**
[figure not shown]
Hybrid VR exposure hierarchy example: Shopping Centre template. Example of VR hierarchy exposure levels (left) based on the shopping center template. The participant is exposed to the exposure environments via the VR headset while concurrently speaking with their therapist (cognitive behavioral therapy for psychosis) and receiving neurofeedback of high β band activity via a visual display of a thermometer (right). VR: virtual reality.

### Implementation Phase (Weeks 3-14)

The implementation phase will consist of weekly sessions delivered over a 12-week period (SD 14 days, Figure 2) and consists of the following two components: (1) CBT in vivo (in response to the VR exposure) and (2) neurofeedback simultaneously presented to the participant via the VR device. The VR apps and sessions can only be accessed by the clinician and administered in person. During these weekly sessions, the therapist will be able to view the VR scenario (via an external monitor) and the neurofeedback thermometer, hear the auditory input, and provide guided assistance to the individual.

### Cognitive Behavioral Therapy in Vivo (in Response to VR Exposure)

The participant will start at the lowest level of their exposure hierarchy and progressively work up the hierarchy over the course of the sessions. The standard approach in ERP interventions will be adopted, which is to achieve a reduction in subjective units of distress to 30/100 before progressing to the next step in the hierarchy. While the participant is exposed to the symptom-eliciting VR scenario, they will engage in CBTp with their therapist (the participant will be wearing “open backed” headphones, allowing them to hear the therapist as well as sounds coming from the VR environment). The CBT will be standard, manualized CBT for voices [64,66,67] dealing with the “hot” cognition reactions elicited by the VR scenario. Key elements include reassurance regarding lack of threat, challenging appraisals of AVH (eg, their perceived power, threat, or dominance; reducing submissive or reactive behaviors), actively responding to AVH, and developing a sense of control over AVH by attempting to delay or reduce their volume or distract from them with a variety of strategies (eg, humming and visualization). Sessions will last 30-45 minutes and will be stopped at any point if requested by the participant.

### Neurofeedback Simultaneously Presented to Participant Via the VR Device

While the participant is being exposed to the VR scenarios and engaging in CBT with a therapist, they will receive visual neurofeedback of electrophysiological activity (power) in the high β band (18-30 Hz) range as measured via EEG. The neurofeedback will be provided to the participant via a single visual image of a thermometer in the corner of the VR scene (ranging from 0 to 100 “degrees”). The temperature of this thermometer is based on the individual’s “baseline” neural activity within the high β band range which is measured at the start of each session prior to entering the VR scenario. The thermometer will increase in “temperature” if high β band power increases. The therapist will inform participants that this thermometer is a visual representation of their current stress levels which will give them a real-time objective indication of how their brains are reacting to the Hybrid therapy. Participants will be instructed to keep their eyes open (so as to remain exposed to the VR scenarios) and to keep the thermometer below the 50-degree reading (ie, “half way”; regulating their neural activity in the desired direction) as an additional motivating goal. In keeping with other neurofeedback studies [18], they will be instructed to devise their own strategy for modulating this neural activity but will be informed that they can discuss different strategies with their therapist. If the thermometer measurement is maintained in the lower half ≥50% of the session time, participants will be made aware of the success of their efforts as positive reinforcement at the end of each of their weekly sessions.

### Integration of Multiple Technologies in One Innovative Treatment Package

Combining the treatment components in Hybrid will engage multiple treatment targets and possible pathogenic mechanisms (psychological, neurophysiological, and neurobiological) simultaneously. There is also likely to be a synergistic effect through the interaction of the individual treatment components that will make the package more than the sum of its parts. To illustrate, the real-time neurofeedback provided to participants and therapists in response to the VR exposure exercises will feed into the content of the CBT therapy, because the participant and therapist will be able to discuss the direct impact the exposure exercises are having in an immediate, non-retrospective fashion. This preserves the benefits of dealing with “hot” cognitive and affective reactions. In turn, the CBT will assist the young person in developing strategies for modulating their neural activity in response to the VR exposure exercises. Moreover, the neurofeedback will dynamically reinforce and boost the effect of CBT via participants being able to see in real time that the CBT is helping change their brain activity. This will create a salient and durable learning experience, contributing to a “real world” transfer effect and motivating the use of CBT skills in the absence of neurofeedback. This tridirectional impact of the treatment components—the way the individual items work together—will amplify their individual contribution to therapeutic gain.

### Measures

#### Primary Outcomes

##### Feasibility and Acceptability of the Hybrid Model

A Pilot Study Assessment Instrument developed by Orygen researchers based on the user experience approach will assess (1) acceptability, (2) helpfulness, (3) engagement, and (4) perceived safety. Items are rated on a self-assessed 5-point Likert scale. Acceptability and feasibility will also be determined by assessing consent and completion rates, the number of sessions attended, the number of dropouts, and completion rates of measures. A high rate of elicited AVH is required to facilitate “hot” cognitions so that the symptoms are targeted directly rather than through abstract self-reflection.

##### Safety of the Hybrid Model

Safety will be assessed by recording adverse events or serious adverse events.

##### Usability of the Hybrid Model

Assessing the experience and usability of the VR environments was conducted using the user experience survey, a specifically adapted 18-item questionnaire from other Orygen VR studies for this study. This measure will be completed at the end of the Hybrid intervention (week 14 of the study). At this point, participants will also complete a semistructured interview about their experience of the intervention and suggestions for modifications to the treatment package.

##### Threshold of the Hybrid Model

Our decision to move on to efficacy trials will be based on the user experience survey, which uses a 5-point Likert scale. We will require at least 70% of our participants to rate 3 and above (which corresponds to agree or strongly agree) that the intervention package was acceptable, feasible, and safe.

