**Objective:**

The aims of this pilot study are to investigate the feasibility, acceptability, safety, and usability of Hybrid treatment (primary aim); and to explore Hybrid’s treatment efficacy and engagement of treatment targets (secondary aim). The primary aim will be assessed via face-to-face user experience surveys on a (self-assessed) 5-point Likert scale (and qualitative open-ended questions) examining: (1) acceptability, (2) helpfulness, (3) engagement, and (4) perceived safety. We will also examine consent and completion rates, and the number of sessions attended. Our threshold for moving on to efficacy trials will be at least 70% of our participants to rate 3 and above (which corresponds to agree or strongly agree) that the intervention package was acceptable, feasible, and safe. The secondary aims will be assessed by observing whether individuals achieve self-directed modulation of high-β neurophysiological activity (neural target) and progression upwards through the VR-based exposure hierarchy (psychological target), and by assessing symptom change scores. This study developed a new treatment approach for auditory verbal hallucinations, a major symptom of psychotic disorders, that integrates advances in psychological therapy (cognitive behavioral therapy for psychosis), technology (virtual reality, VR), and neuroscience (electroencephalography-based neurofeedback).

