### Planned Analyses

As this study is a pilot study designed to generate initial data to guide future research, a power calculation has not been conducted. A sample size of 10 participants is consistent with similar proof-of-concept and pilot studies [44,48].

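### The go/no-go cut-off of 3 on a 5-point scale conflicts with its own verbal definition if items are coded 1-5, and the article does not state the coding that would reconcile them

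*Protocol article*

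**What the plan says.** The rule stands in the protocol article under Methods, Primary Outcomes, Threshold of the Hybrid Model. That section first names the instrument: "Our decision to move on to efficacy trials will be based on the user experience survey, which uses a 5-point Likert scale". It then sets the bar: "We will require at least 70% of our participants to rate 3 and above (which corresponds to agree or strongly agree". The attributes to be endorsed are that the package was acceptable, feasible and safe.

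The Objective paragraph of the Abstract gives the same bar with the same explanation: "at least 70% of our participants to rate 3 and above (which corresponds to agree or strongly agree".

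The Usability section describes the user experience survey as an adapted 18-item questionnaire completed at week 14. It gives neither category labels nor numeric coding. The Feasibility and Acceptability section describes another instrument, the Pilot Study Assessment Instrument, in similar terms ("Items are rated on a self-assessed 5-point Likert scale"), also without labels or coding.

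On size, Planned Analyses says "A sample size of 10 participants is consistent with similar proof-of-concept and pilot studies" and that "a power calculation has not been conducted".

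**The concern.** The threshold is given twice over, once as a number and once in words, and the two should select the same answers. On the common 1-5 coding they do not. The number admits the middle category and the words leave it out. A reader applying the number and a reader applying the words would then count different people as endorsing the package.

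This is the only progression criterion in the article with a figure attached. The study is single-arm and unblinded, and five people had already been included by February 2025. If the mismatch remains when the ratings come in, the reading could be chosen with the answers in view, and the threshold would no longer be fixed in advance.

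**Working it through.** **Inputs from the article.** Five response categories; cut-off of 3 or more; two categories named in words; required share 70%; N = 10. There is no power or error-rate calculation to reproduce.

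**Step 1: the bar in people.** 0.70 × 10 = 7, so at least 7 of 10 must endorse.

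**Step 2: count the categories.**

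| Coding | Scores of 3 or more | Categories admitted | Categories named in words | Match |
|---|---|---|---|---|
| 1-5 | 3, 4, 5 | 3 | 2 | no |
| 0-4 | 3, 4 | 2 | 2 | yes |

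**Step 3: does the reading change the decision?** For one item, with independent answers and endorsement probability p,

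P(go) = Σ over k = 7 to 10 of C(10,k) p^k (1−p)^(10−k).

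For p = 0.40 the four terms are 0.0425 + 0.0106 + 0.0016 + 0.0001 = 0.0548. The other values needed are 0.0106 (p = 0.30), 0.1719 (0.50), 0.3823 (0.60), 0.6496 (0.70) and 0.8791 (0.80).

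The response distribution is not in the documents. The shares below are assumptions, applied to a form coded 1-5. Counting 4 or more uses p = share agreeing or better. Counting 3 or more adds the midpoint share.

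| Agree or better | Midpoint | P(go), 3 or more | P(go), 4 or more |
|---|---|---|---|
| 60% | 10% | 65.0% | 38.2% |
| 60% | 20% | 87.9% | 38.2% |
| 50% | 20% | 65.0% | 17.2% |
| 50% | 30% | 87.9% | 17.2% |
| 40% | 20% (uniform answers) | 38.2% | 5.5% |
| 40% | 30% | 65.0% | 5.5% |
| 30% | 40% | 65.0% | 1.1% |

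In three of these rows the share agreeing or better varies while the share scoring 3 or more is the same 70% as in the last row. In those four rows the literal rule passes 65.0% of the time, while the worded rule passes between 1.1% and 38.2% of the time.

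The gap depends on the mix. With 30% agreeing and 10% at the midpoint it is small, 5.5% against 1.1%. With 40% and 40% it is 87.9% against 5.5%.

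**Step 4: the other coding.** On a 0-4 form both readings count the same two categories, so P(go) is identical and the difference is zero.

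All figures are per item. Requiring all three attributes jointly could only lower them or leave them unchanged.

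**The case against.** The strongest reply is that the article states 1-5 coding no more than it states 0-4. Under 0-4 the number and the words agree exactly, and the same explanation appears in two places, which may itself point to that coding. Item labels and scoring belong to the questionnaire, and a journal article commonly leaves them to the form or the full protocol. This stands, and it limits the point. Missing labels alone would be no finding. What remains is that the article states a decision threshold as a number plus a definition, and a reader cannot tell whether they match.

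Two stronger readings are tempting. A reader might infer that neutral answers will in fact count as endorsement. That needs both 1-5 coding and a neutral midpoint, and the documents give neither. A reader might also infer that the package would pass with most participants neutral. The assumed distributions do not show this, since the midpoint never exceeds 40% in any of them.

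Nor is the survey percentage the only evidence to be considered. The Abstract's Conclusions make progression depend on favorable evidence across acceptability, feasibility, safety and usability. Primary Analyses also plans review of adverse events, thematic analysis of interviews, and the percentages at different rating levels on the Pilot Study Assessment Instrument. The survey rule is nevertheless the only criterion with a number.

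A confidence interval beside the percentage is a separate reporting choice that can be left to the analysis plan. It would not measure this mismatch.

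**Conclusion.** The point holds conditionally. On 1-5 coding the cut-off and its verbal definition contradict each other; on 0-4 coding they agree; the article does not say which applies. The intended meaning, endorsement by the top two categories, is stated consistently, so the doubt attaches to the number.

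The consequence can be decisive at 7 of 10. In the seven tabulated distributions, the per-item chance of a go differs between the two readings by about 27 percentage points (64.96 − 38.23 = 26.7) to about 71 (87.91 − 17.19 = 70.7). These sizes rest on assumed response shares, independent answers, 10 raters and 1-5 coding. Under 0-4 coding the effect is nil. That neutral answers are being counted as agreement is not established.

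**What to change.** In both the Abstract's Objective and the Threshold section, define endorsement by its label, *agree or strongly agree*, and give the score that corresponds on the actual form: 4 or 5 if it is coded 1-5, or 3 or 4 if it is coded 0-4. Keep all three attributes: acceptable, feasible and safe. Make the change before the ratings are analysed. The sponsor holds the questionnaire and can settle the coding by looking at it.

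The cost is one sentence in each place, with no change to sample, visits or treatment. The downside is that, if the form is coded 1-5, the bar is harder to pass than under the number as printed. If it is coded 0-4, the bar does not move.

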#### Secondary Outcomes

##### Auditory Verbal Hallucinations

The hallucinations scale of the Psychotic Symptom Rating Scales will be used to assess changes in AVH severity, frequency, and distress.

##### General Psychopathology

The Brief Psychiatric Rating Scale [68], Structured Clinical Interview for the *DSM-5* (*Diagnostic and Statistical Manual of Mental Disorders* [Fifth Edition]) [69], Social and Occupational Functioning Assessment Scale (SOFAS) [70], and the Positive and Negative Syndrome Scale (PANSS) [71] will be used to assess change in general psychopathology and symptoms.

##### Psychological Treatment Target

The highest level in exposure hierarchies was achieved in each session. For each participant, the final target score of each of these measures will be the average over the 12 implementation phase sessions.

##### Neuropsychological Treatment Target

This will be operationalized as the difference (ie, change) between the first half and the second half of the VR exposure exercises in average power of high β band activity. A mean score will be used for analysis and will be given by the average change in ratings over the sessions attended.

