#### Target Scores

Means, SDs, and 95% CIs of neural (average β band power) and psychological (exposure hierarchy level) target scores will be reported. The magnitude of the changes in both scores will reflect the degree of target engagement achieved. A mean score will be used for analysis and will be given by the average change over the first half (mean of weeks 3 to 8) and second half (mean of weeks 9 to 14) of the sessions attended.

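### The neural target score is a half-to-half change with no stated baseline reference, so sustained down-regulation of high-β power scores about zero, the same as no regulation

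*Protocol article*

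**What the plan says.** Four parts of the protocol article bear on this score.

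- **Neuropsychological Treatment Target** (Secondary Outcomes) defines it, for mean high-β power, by "the difference (ie, change) between the first half and the second half of the VR exposure exercises". The value analysed is "given by the average change in ratings over the sessions attended". Neither a baseline nor an order of subtraction is mentioned.
- **Target Scores** (Secondary Analyses) describes, for attended sessions, a mean score "given by the average change over the first half (mean of weeks 3 to 8) and second half (mean of weeks 9 to 14"), and adds: "The magnitude of the changes in both scores will reflect the degree of target engagement achieved".
- **Neurofeedback Simultaneously Presented to Participant Via the VR Device** scales the thermometer to "neural activity within the high β band range which is measured at the start of each session prior to entering the VR scenario". Participants are asked to stay under 50 degrees. They are told at the end of the session that they succeeded under this condition: "If the thermometer measurement is maintained in the lower half ≥50% of the session time".
- **Further Analyses** relates engagement of the neural and psychological targets to change in the clinical measures.

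The Objective in the abstract gives the purpose: to see whether individuals achieve self-directed modulation of high-β activity.

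**The concern.** Participants are trained and rewarded on a level held below a reference for as long as possible. The outcome records only how much power differs between two periods. A participant who brings β down at once and keeps it there achieves what was asked, yet has two equal halves.

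The score therefore cannot separate sustained success from no regulation at all, although the plan reads its size as engagement. Because only magnitude is interpreted and no sign is fixed, a participant whose β rises could also be read as engaged.

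The neural half of the proof of concept rests on this number, and it is carried into the exploratory association with clinical change. With 10 participants, a few misread as unengaged could change what that analysis appears to show.

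**Working it through.** The article gives no β-power values and no numerical result for this score, so there is no figure to reproduce. The check applies the stated definitions to simple profiles. All power values are assumptions, in units where the session's pre-VR baseline is 1.0.

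**1. Halves taken within the exposure.** Let H1 and H2 be mean high-β power in the two halves. The stated score is H1 − H2, or H2 − H1, since the order is not given. Two baseline-referenced scores are shown for comparison: 1.0 − (H1 + H2)/2, and ln[(H1 + H2)/2 ÷ 1.0].

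| Profile | H1 | H2 | H1 − H2 | Baseline − mean | Log ratio |
|---|---|---|---|---|---|
| Suppressed throughout | 0.7 | 0.7 | 0.00 | +0.30 | ln 0.70 = −0.36 |
| Slow regulator | 1.0 | 0.7 | +0.30 | +0.15 | ln 0.85 = −0.16 |
| Flat at baseline | 1.0 | 1.0 | 0.00 | 0.00 | ln 1.00 = 0.00 |
| Worsening | 1.0 | 1.3 | −0.30 | −0.15 | ln 1.15 = +0.14 |
| Flat above baseline | 1.3 | 1.3 | 0.00 | −0.30 | ln 1.30 = +0.26 |
| Spike, partial fall | 1.6 | 1.1 | +0.50 | −0.35 | ln 1.35 = +0.30 |

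The first, third and fifth rows are indistinguishable on the stated score. The slow regulator outscores the one who succeeded from the start. By magnitude alone, the slow regulator and the worsening participant tie at 0.30. Both baseline-referenced columns put the first row best and separate all six.

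**2. Halves taken as weeks 3-8 and weeks 9-14.** With 12 weekly sessions, the score is the mean of sessions 1-6 minus the mean of sessions 7-12.

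- 0.7 in every session: 0.7 − 0.7 = 0.000.
- 1.3 in every session: 1.3 − 1.3 = 0.000.
- Linear fall from 1.0 to 0.7: the step is 0.3/11 and the half-means lie six steps apart, so 6 × 0.3/11 = +0.164.
- Linear rise from 1.0 to 1.3: −0.164.

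The zero for sustained suppression therefore remains.

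**3. The two readings measure different things.** A fall of 0.30 within every session, with no change from session to session, scores 0.30 on the first reading and 0 on the second. The week-based contrast is also mixed with exposure level. The section on cognitive behavioral therapy in vivo starts participants at the lowest step and moves them up over the sessions, so later weeks tend to be more provoking.

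**4. Would normalising the halves help?** Dividing both by the same session baseline B gives (H1 − H2)/B, which is still zero when H1 = H2. In a log ratio of the halves, ln[(H1/B)/(H2/B)] = ln(H1/H2), so B cancels.

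**The case against.** A fall in β during exposure, after an initial reaction to the scene, is a legitimate way to define modulation in a treatment built on provoking a response and then reducing it. The 50-degree goal is described as a motivating aid and the time rule triggers feedback; neither is declared an outcome. An outcome that differs from a training cue is not in itself a contradiction. The measure is secondary, the association analysis is exploratory, and the decision to proceed to efficacy trials rests on the user experience survey. All of that stands, and it limits the weight of the point. It does not answer the fact that a change score is to be read as degree of engagement while giving zero to sustained control.

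A reader might go further and infer that failing regulators score highest, or that the ranking is generally reversed. The documents do not support this. In the table a flat failure scores zero, and a worsening participant is lowest under first minus second. Only the selected spike-and-fall profile is highest while staying above baseline.

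A smooth model shows the same limit. Assume β(t) = 0.8 + 0.6·exp(−t/τ) over 40 minutes, baseline 1.0, 50 degrees equal to baseline. Then H1 − H2 = 0.6·(τ/20)·(1 − exp(−20/τ))². This is 0.060 at τ = 2 and peaks at about 0.244 near τ = 16. There, power is below baseline once t exceeds τ·ln 3 = 17.6 minutes, or 56% of the time, which meets the feedback rule. It then falls to 0.186 at τ = 40 and 0.054 at τ = 200; in both of these β never gets below baseline within the session. So the score is not monotone in success, but neither does it systematically reward failure.

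Nor does the article say that power is unnormalised. It states no normalisation and excludes none, and the full protocol or analysis plan may specify one. Step 4 of the check shows that the point does not depend on this.

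**Conclusion.** The point holds as a mismatch between the stated score and the reading placed on it. Sustained suppression and no regulation both score about zero, under either definition of the halves and with or without scaling to the session baseline. That result is algebraic and needs no assumed values. That a slower regulator can outscore an immediate one (0.30 against 0.00 in the example) depends on the profile; the example shows that it can happen, not how often.

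Two defects of definition accompany it. No direction is fixed while magnitude is interpreted. The outcome and analysis sections also appear to place the halves differently; the outcome wording could be stretched to mean the whole series of exercises, but averaging changes over sessions attended points to a within-session contrast. The passages need to be reconciled.

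This should be changed before analysis. It affects a secondary proof-of-concept measure and the exploratory mechanism analysis, not the primary aims or the progression rule.

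**What to change.** - Define the neural target score per session as the log of mean high-β power (18-30 Hz) during exposure divided by the same session's pre-VR baseline, averaged over sessions attended. State that negative values mean down-regulation.
- Report beside it the percentage of session time below 50 degrees. The article does not say where baseline sits on the 0-100 scale, so this is not simply the same measure again.
- Report the pre-VR baseline over sessions, so that a general fall in β is not hidden by resetting the reference each week.
- Keep the half-to-half change as a supplementary learning measure. State its sign, and reconcile Neuropsychological Treatment Target with Target Scores on what the halves are. If the week-based contrast is kept, show the exposure level reached alongside it.
- Name in Further Analyses which neural score enters the association with clinical change.

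The cost is wording in the outcome and analysis sections. The baseline and the thermometer reading are already generated each session; the article does not say that they are stored, so this should be confirmed. The one statistical drawback is that the ratio carries the noise of the baseline recording.
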